## Abstract

**Background:**

Chronic pancreatitis is an inflammatory disease which is characterized by an irreversible conversion of pancreatic parenchyma to fibrous tissue. Beside obstructive jaundice and pseudocyst formation, about half of the patients need surgical intervention due to untreatable chronic pain during the course of the disease. In most of the patients with chronic pancreatitis, the head of the pancreas is the trigger of the chronic inflammatory process. Therefore, resection of pancreatic head tissue must be the central part of any surgical intervention. However, it is unclear to which extent the surgical procedure must be radical in order to obtain a favourable outcome for the patients.

**Design:**

A single centre randomized controlled, superiority trial to compare two techniques of duodenum preserving pancreatic head resection. Sample size: 65 patients will be included and randomized intraoperatively. Eligibility criteria: All patients with chronic pancreatitis and indication for surgical resection and signed informed consent. Cumulative primary endpoint (hierarchical model): duration of surgical procedure, quality of life after one year, duration of intensive care unit stay, duration of hospital stay. Reference treatment: Resection of the pancreatic head with dissection of the pancreas from the portal vein and transsection of the gland (Beger procedure). Intervention: Partial Resection of the pancreatic head without transsection of the organ and visualization of the portal vein (Berne procedure).

Duration: September 2003-October 2007.

**Organisation/responsibility:**

The trial is conducted in compliance with the protocol and in accordance with the moral, ethical, regulatory and scientific principles governing clinical research as set out in the Declaration of Helsinki (1989) and the Good Clinical Practice guideline (GCP). The Center for Clinical Studies of the Department of Surgery Heidelberg is responsible for planning, conducting and final analysis of the trial.

## Background

### Medical problem

Chronic pancreatitis is an inflammatory disease, which is characterized by progressive and irreversible destruction of pancreatic parenchyma and transformation into fibrous tissue. The leading symptom of chronic pancreatitis is chronic pain, which requires surgical intervention in about 50% of the patients [1].

Despite of the fact that the etiopathogenesis of pain in chronic pancreatitis is not fully understood, the concept of a neuroimmune interaction in the head of the pancreas is in accordance with the observation that simple drainage procedures seldom lead to satisfactory pain relief in the long run in patients with an enlarged pancreatic head [2-6]. Only surgical techniques that include resection of the inflammatory mass in the pancreatic head have shown to be successful in the treatment of this disease [7,8].

### The Beger procedure (reference treatment)

In 1972, H.G. Beger for the first time described the technique of duodenum preserving pancreatectomy in the treatment of patients with chronic pancreatitis (Fig. 1) [9,10]. The rationale of this intervention is the resection of the inflammatory mass in the pancreatic head without large loss of unaffected parenchyma and maintenance of the duodenal passage. Different studies have shown that this organ preserving technique is at least as effective as the more radical Kausch-Whipple procedure (pancreatico-duodenectomy) regarding pain control (effective pain diminishing in >80% within 5 years), but postoperative morbidity and the incidence of diabetes mellitus are lower [1,11-13].

**Figure 1 F1:**
[figure not shown]
**Beger procedure (reference treatment)**. Reconstruction after duodenum preserving pancreatic head resection with a Roux en-Y jejunal loop as side-to-end and side-to-side pancreatico-jejunostomy.

### The Berne procedure (selection of intervention)

Over the years, different variations of the duodenum preserving technique have been introduced. In 1985, Frey and Smith described a modification in which a longitudinal pancreatico-jejunostomy is combined with a local resection of the pancreatic head [14,15]. This technique combines the principle of duodenum preserving pancreatic head resection with the drainage of the main pancreatic duct. In 1998, similar to the Frey technique, Izbicki et al. combined the duodenum preserving resection of the pancreatic head with a V-shaped incision of the body of the pancreas in order to also reach II° and III° pancreatic side branches. The results obtained with this technique are very similar to the original Beger technique. Thirty patients were operated without mortality. After a median follow up of 30 months, 92% of the patients were pain free with preserved endocrine and exocrine function [16].

The main advantage of these variations of the original Beger procedure lies in the fact that the dissection of the pancreas from the portal vein can be avoided, which is regarded as the most hazardous part of the intervention [4]. Especially in case of portal vein thrombosis, the division of the pancreatic body from the portal vein, which is an essential step in the Beger (and also Kausch-Whipple) procedure, can be very demanding. Bleeding from the portal vein in this situation can be extremely difficult to control.

To combine the advantages of the original Beger procedure with the Frey technique, we developed an additional modification which consists in a duodenum preserving resection of the pancreatic head in analogy to the original Beger technique, with the difference that a small shape of pancreatic tissue remains on the anterior wall of the portal vein in a way that the hazardous division of vein and pancreatic body is avoided (Fig. 2) [17].

**Figure 2 F2:**
[figure not shown]
**Berne procedure (intervention)**. Reconstruction after duodenum preserving pancreatic head resection with a Roux en-Y jejunal loop as side-to-side pancreatico-jejunostomy.

## Study design

### Aim of the study

The objective of this trial is to compare two different surgical techniques for the treatment of chronic pancreatitis with regard to complication rates, length of operation, length of intensive care treatment, length of hospital stay, exocrine/endocrine pancreatic function and quality of life.

### Number of patients needed

As estimated effect size a difference of mean operating time of one hour between the two groups and a variability of this difference in between the expected absolute effect (standard deviation of one hour) is defined. Groups of 22 patients each would permit the verification of the null-hypothesis with an α-error set at 0.05 and a β-error at 0.10, yielding a power of 90%.

To evaluate the true efficacy of the Berne procedure a per protocol analysis is necessary. For the external validity of the study an intention to treat approach for analysis is requested. Due to the nature of complex surgery such as a pancreatic resection it can be expected that one third of all randomised patients will not receive the intended procedure. Therefore at least 65 patients should be randomised.

## Eligibility criteria

### Inclusion criteria

• Patients of any age (>18 ys)

• Expected survival time more than 24 months

• Informed consent

### Exclusion criteria

• Participation in another intervention trial that would interfere with the intervention and outcome of this study

• Severe psychiatric disorders or neurological diseases

• Lack of compliance

• Drug and/or alcohol abuse according to local standards

### Ethics, study registration and consent

The final protocol was approved by the independent ethics committee of the University of Heidelberg. The study was registered at Current Clinical Trials (ISRCTN No. 50638764). Patients who are scheduled for duodenum preserving pancreatic head resection had a pre-treatment visit to give the informed consent. During this visit the patient will be screened and informed about the trial. In the course of the conversation, the study procedure, risks, benefits and data management will be clarified in detail.

## Randomisation and procedures for minimising bias

### Minimising systematic bias

In order to achieve comparable groups for known and unknown risk factors, randomization will be performed. The random allocation sequence was generated by a free available randomization software tool [18] by a trained independent study nurse not further involved in this trial. She also prepared the sealed and opaque envelopes for the randomisation procedure in the operation theatre. The sealed randomization list was stored in the investigator file. A sufficient number of patients will be recruited according to the sample size calculation in order to prevent random error. Patients will get randomised intra-operatively by an independent study nurse or anaesthesiologist once the surgeon decides that clinical equipoise is given, usually after the pancreas has been prepared and mobilised (Kocher's maneuver). All interventions will be done as described below. Patients in whom the randomised procedure cannot be performed due to technical or anatomical reasons will be analysed according the intention to treat principle.

### Minimising treatment bias

The participating surgeons are all experienced in pancreatic surgery. Annually more than 300 resections of the pancreas are performed in Heidelberg. Both procedures used in this trial are supervised by two authors ([name], [name]) in order to guarantee correct execution according to the protocol (intraoperative surgical monitoring). Concomitant treatment will be equal for both groups including antibiotic prophylaxis, use of sandostatin and anaesthesia.

### Minimising measurement bias

An independent study nurse will document and monitor the procedure in the operating theatre. Blinding in this phase of the trial is not possible due to the research question.

Standardized patient interviews will be performed by blinded study nurses 6, 12 and 24 months after surgery, using EORTC QLQ-C30 questionnaire and the disease specific module for pancreatic diseases EORTC QLQ-PAN26 [19,20].

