## Primary and secondary endpoints

### Primary endpoints

The primary endpoint is combined out of four components. In order to adjust for multiple testing a hierarchical model is used.

1. Duration of surgical procedure [min]

2. Quality of life (EORTC QLQ-C30 questionnaire and the disease specific module for pancreatic diseases EORTC QLQ-PAN26) at 12 months after the intervention

3. Duration of stay on the intensive care unit

4. Duration of postoperative hospital stay

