**Figure 3 F3:**
[figure not shown]
**Flow chart**. If the null hypothesis of no difference can be rejected the other components can be tested in a hierarchical way.

1. The test of H_0,2 _*Quality of life in both groups is not equivalent *is an equivalence test. Based on preliminary experiences with the EORTC QLQ-C30/PAN26 questionnaires in pancreatic cancer patients [20], we estimated baseline raw score values in the range of about 60 (SD 25) before therapy. When transformed into a percentage scale (with 100% indicating perfect health) this represents values of 45% (SD 18%). After surgery, quality of life can be estimated to improve up to value of 75% (SD 18%). We assume equivalence for the two resection techniques, if the two-sided 95% confidence intervals for difference in quality of life fall within the interval of +/-15%. The value of 15 as delta was chosen, because the overall effect of surgery is in the range of about 30 percentage points. Therefore, the minimal clinically relevant difference can be estimated by halving this effect of surgery. To show equivalence for a delta of 15 (SD 18) with alpha = 5% and beta = 20%, a sample size of 60 patients is required [22].

2. The test of H_0,3 _*Length of stay on the intensive care unit of both groups is not equivalent *is an equivalent test on the level of 5%. The zero-hypothesis is declined if the 90% confidence interval for the difference of mean values of ICU stay in hours for both groups is in between [-12/12 hours].

3. The test of H_0,4 _*Hospital stay on both groups is not equivalent *is an equivalent test on the level of 5%. The null-hypothesis is declined if the 90% confidence interval for the difference of mean hospital stay in days for both groups is in between [-2/2 days].

Once the null hypothesis cannot be rejected no further testing is applied. All secondary endpoints will be analyzed using descriptive and graphical methods.

Safety-related data will be analyzed with respect to frequency of:

• Severe bleeding intra- or postoperatively requiring blood transfusion

• Laparotomy

• Pancreatic fistula

• Pulmonary infection and wound infection are secondary endpoints, but are also defined as adverse events. Severe intraoperative bleeding with need for blood transfusion will even always be considered a serious adverse event.

Safety-related data will be analyzed with respect to frequency of:

• Serious adverse events and adverse events stratified according to the organ-systems

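### No pre-operative quality-of-life score is listed and the 12-month equivalence rule has no baseline term; a baseline-adjusted analysis would gain precision by an amount that depends on an unstated correlation

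*Protocol article*

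**What the plan says.** - **Schedule.** The subsection on minimising measurement bias states: "Standardized patient interviews will be performed by blinded study nurses 6, 12 and 24 months after surgery". It names the EORTC QLQ-C30 and the PAN26 module. No pre-operative time point is listed.
- **Endpoint.** Under Primary endpoints, quality of life "at 12 months after the intervention" is the second of four hierarchical components.
- **Decision rule.** Under Analysis, equivalence is assumed "if the two-sided 95% confidence intervals for difference in quality of life" "fall within the interval of +/-15" percentage points. No model or covariate is named. Testing stops at the first null hypothesis that is not rejected, so H0,2 gates H0,3 (intensive care stay) and H0,4 (hospital stay).
- **Margin.** From experience with the questionnaires in pancreatic cancer patients, "we estimated baseline raw score values in the range of about 60 (SD 25) before therapy", which the plan converts to 45% (SD 18%). It expects 75% (SD 18%) after surgery and takes half of that 30-point change as the margin.
- **Sample size.** For a margin of 15 and SD 18, with alpha 5% and beta 20%, "a sample size of 60 patients is required". At least 65 are to be randomised (Number of patients needed).
- **Opportunity.** Patients "had a pre-treatment visit to give the informed consent" (Ethics, study registration and consent). Randomisation takes place later, in the operating theatre (Minimising systematic bias; Study treatment).

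**The concern.** The plan uses a pre-surgery score to justify its margin but lists no occasion on which that score is measured in this trial. Two things follow.

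First, the H0,2 interval is wider than it need be if pre-operative and 12-month scores are correlated. There is little reserve: 60 patients are required and 65 randomised, so losing more than 5 (5/65 = 7.7%) before 12 months takes the trial below its own requirement. If H0,2 fails only for lack of precision, the two length-of-stay comparisons are not tested either.

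Second, the 30-point gain behind the ±15 margin is borrowed from patients with a different disease. With the listed schedule the trial cannot show whether its own patients gain anything like 30 points, so a reader cannot judge whether 15 is really half the effect of surgery.

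**Working it through.** **Inputs from the Analysis section:** margin 15; SD 18; two-sided 95% interval, i.e. two one-sided tests at 0.025 each; power 80%; N = 60. True difference 0 and equal allocation are taken for the calculation.

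**Assumed, because the documents give no value:** correlation r between baseline and 12-month score, from 0.2 to 0.7.

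**1. The plan's own figure.** n per arm = 2 × [SD × (z(0.975) + z(0.90)) / margin]² = 2 × [18 × (1.960 + 1.282) / 15]² = 30.26, or 60.5 in total (62 if each arm is rounded up). The stated 60 reproduces. It is the figure for an analysis that makes no use of a baseline score.

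**2. Unadjusted power with 30 per arm.** Standard error = 18 × √(2/30) = 4.65. Normal approximation: 2 × Φ(15/4.65 − 1.96) − 1 = 79.5%. Allowing for the estimated SD (t-based, 58 degrees of freedom): 77.5%.

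**3. Power with baseline ANCOVA.** Replace the SD by 18 × √(1 − r²) and give up one degree of freedom. For example, r = 0.4 gives 18 × √0.84 = 16.5.

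| r (assumed) | t-based power, 60 evaluable | Gain over 77.5% (points) | Total N for 80% power (normal approximation) |
|---|---|---|---|
| 0.2 | 79.9% | 2 | not computed |
| 0.3 | 82.8% | 5 | 56 |
| 0.4 | 86.7% | 9 | 52 |
| 0.5 | 91.1% | 14 | 46 |
| 0.6 | 95.5% | 18 | 40 |
| 0.7 | 98.7% | 21 | 32 |

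The last column compares with 62 unadjusted, rounded the same way.

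**4. With loss to follow-up.** The documents give no loss rate. Assuming 20%, 65 × 0.8 = 52 patients are evaluable. Unadjusted power is then 67.6%; with adjustment it is 74%, 79% and 85% at r = 0.3, 0.4 and 0.5.

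**5. Chance imbalance.** With 32 and 33 patients and SD 18, the standard error of the baseline difference is 18 × √(1/32 + 1/33) = 4.47. An imbalance beyond 5 points then has probability P(|Z| > 5/4.47) = 0.26. With equal SDs before and after, the expected carry-over into the 12-month difference is r × imbalance: 1.5 to 2.5 points for r = 0.3 to 0.5. For scale, the unadjusted 95% half-width with 60 patients is about 2.00 × 4.65 = 9.3, which leaves 15 − 9.3 = 5.7 points for the observed difference.

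**The case against.** The strongest reply is that this reads an omission into a condensed article. The schedule sentence concerns blinded interviews after surgery. A questionnaire completed before randomisation has no allocation to blind, so that sentence need not mention it. A baseline table is planned with its contents unlisted, and covariate adjustment commonly belongs to an analysis plan that is not shown. This stands in part. A reader might infer that baseline quality of life is not collected, or that adjustment is ruled out; the article says neither. It supports only that no baseline score is listed and no baseline term is stated. But the article does set out the interview times, the decision rule and the basis of the margin, and on those terms the improvement is available.

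Other stronger readings also fail:

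- **That the 12-month comparison is biased or invalid, or that 60 is wrong.** Randomisation makes the unadjusted difference valid, and 60 reproduces. The pre-surgery score enters only the rationale for the margin.
- **That the gain in power is a fixed figure.** A gain of 9 to 14 points, for instance, needs r of 0.4 to 0.5, and nothing in the documents favours that range. Major surgery and an expected 30-point shift between the two measurements could well weaken the correlation.
- **That a baseline imbalance passes in full into the result.** It does so only in proportion to r. It is also already part of the 12-month variance, so it is the same loss of precision seen another way, not an additional one.
- **That an observed gain other than 30 would change the test.** The margin is prespecified; the observed gain bears only on how the result is interpreted.

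**Conclusion.** The point holds as a cheap improvement, not as an error in the plan. On the listed schedule and stated rule, H0,2 makes no use of a pre-operative score, although one could be obtained before allocation. With 60 evaluable patients, t-based power is 77.5% unadjusted and about 80% to 99% with baseline ANCOVA for an assumed r of 0.2 to 0.7, a gain of about 2 to 21 points. At the low end the benefit is slight. At r = 0.4 or above it would offset the loss of several patients.

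These figures rest on SD 18 at both time points, a true difference of zero, equal arms and the assumed correlation. The second benefit does not depend on the correlation: a baseline score would let the trial compare its own gain with the 30 points that justify the margin.

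**What to change.** 1. Give the same two questionnaires at the existing pre-treatment visit, before intraoperative randomisation. If the full protocol already does so, state it; then only items 2 and 3 apply.
2. Base the H0,2 95% confidence interval on the 12-month treatment difference from an ANCOVA with the baseline score as covariate, keeping the ±15 margin. A plain change-from-baseline comparison is not a substitute: by the normal approximation with 60 patients its power is 55.7% at r = 0.3, and it only equals the unadjusted 79.5% at r = 0.5.
3. Report the observed mean gain from baseline to 12 months beside the assumed 30 points.

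The cost is one extra questionnaire set per patient at a visit that already takes place, and one sentence in the analysis section. A pre-operative score cannot be recovered after surgery, so item 1 has to be in place before a patient is operated on.

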## Study treatment

After a midline laparotomy, wide exposure of the pancreas is obtained by opening of the gastro-colic ligament. The duodenum and the pancreatic head are then mobilized by an extended Kocher maneuver. If there are any doubts on the dignity of the pancreatic head tumour, biopsies will be taken and pathological examination will be performed.

After exhibition of the pancreas, the randomisation will be performed using sequentially numbered, opaque, sealed envelopes; according to the allocation, the procedure will be continued.

### Beger procedure (reference treatment)

The pancreas is gently lifted and subtle dissection is performed between the mesenteric vein and the body of the pancreas, taking care to avoid injury to the major retropancreatic vessels and smaller side branches. After this step, multiple stay sutures (4/0 PDS) are placed around the parenchyma of the pancreatic head to assign resection margins. This is important to avoid inadvertent injury to the duodenum and assures that a lamella of pancreatic parenchyma along the loop of the duodenum remains and assures blood supply. The subtotal resection of the pancreatic head starts with the transsection of the pancreas above the portal vein proceeding towards the prepapillary common bile duct. In all phases of the intervention meticulous haemostasis is required. Reconstruction is performed with a Roux-en-Y loop of the jejunum with an end-to-side pancreatico-jejunal anastomosis and another side-to-side anastomosis of the jejunal loop with the remaining hollowed pancreatic head.

### Berne procedure (intervention treatment)

Both the dissection of the pancreatic body from the portal vein and the transsection of the pancreas over the portal vein is not done with the consequence that only one cavity results. Also in this case, multiple stay sutures mark the dissection margin and support blood sparing surgery. After subtotal resection of the pancreatic head, reconstruction is performed in analogy to the original Beger-technique with a Roux-en-Y jejunal loop and side-to-side pancreatico-jejunostomy.

Independently of the type of resection (Beger or Berne procedure), in case of stenosis of the intrapancreatic segment of the common bile duct which cannot be decompressed by resecting the circumferential fibrous tissue or in case of accidental opening of the common bile duct during resection, an additional bilio-digestive anastomosis will be performed.

## Primary and secondary endpoints

### Primary endpoints

The primary endpoint is combined out of four components. In order to adjust for multiple testing a hierarchical model is used.

1. Duration of surgical procedure [min]

2. Quality of life (EORTC QLQ-C30 questionnaire and the disease specific module for pancreatic diseases EORTC QLQ-PAN26) at 12 months after the intervention

3. Duration of stay on the intensive care unit

4. Duration of postoperative hospital stay

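### Operating time, read as the whole operation, includes minutes before the mid-operation randomisation; adjusting the gatekeeper test for them would be a cheap gain in precision

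*Protocol article*

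**What the plan says.** The Primary endpoints section lists "Duration of surgical procedure [min" as the first of four hierarchically ordered components. The Analysis section tests it by Mann-Whitney at the 5% level. Quality of life, intensive care stay and hospital stay are tested only if that null hypothesis is rejected.

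Under Number of patients needed, the sample size rests on this component: "a difference of mean operating time of one hour between the two groups", a "standard deviation of one hour", and an "α-error set at 0.05 and a β-error at 0.10, yielding a power of 90" per cent. The result is "Groups of 22 patients each". It is then raised to 65 because "one third of all randomised patients will not receive the intended procedure".

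Randomisation takes place in theatre. Minimising systematic bias puts it "once the surgeon decides that clinical equipoise is given, usually after the pancreas has been prepared and mobilised". Study treatment describes laparotomy, exposure, an extended Kocher manoeuvre and, where there is doubt, biopsies, and then says: "After exhibition of the pancreas, the randomisation will be performed using sequentially numbered, opaque, sealed envelopes". The same sentence speaks of the procedure carrying on after allocation, so in the article's own usage it has begun by then. No start or stop point for the duration is given.

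**The concern.** Allocation is concealed until the envelope is opened, so the time spent before that moment cannot depend on the assigned procedure. The arms part only afterwards, when the Beger procedure adds dissection from the portal vein, transsection and a second anastomosis. If the clock starts at incision, each patient's outcome is an early part with no treatment signal plus a later part that carries all of it. The early part is not constant: the moment of randomisation is only usually after mobilisation, and only some patients have biopsies.

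At stake is the precision of the test on which the sample size is built and which must succeed before the other three components can be tested.

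**Working it through.** **Inputs from the article.** Difference δ = 60 min; SD σ = 60 min; α = 0.05 (taken as two-sided, which reproduces the stated size; one-sided would give 18 per group); power 90%; one third not receiving the intended procedure; 65 randomised.

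**Inputs assumed.** The article does not give the variance of pre-randomisation time. Let f be its share of the total variance, with f = 10, 20 or 30%, and take earlier and later times as independent.

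**1. The plan's own figure.** n per group = 2(z₀.₉₇₅ + z₀.₉₀)²(σ/δ)² = 2(1.960 + 1.282)² × 1 = 21.01, rounded up to 22. The t-test has 90.0% power at 22 per group. Inflation: 44 / (2/3) = 66, against 65 stated. The stated size reproduces.

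**2. What adjustment removes.** Write total = pre + post, with correlation ρ between the two parts. Regressing total on pre leaves residual variance Var(post)(1 − ρ²). The expected arm difference is unchanged, because pre is fixed before a concealed allocation. With ρ = 0 the residual variance is σ²(1 − f), so the standardised difference becomes d/√(1 − f).

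**3. Power, two-sided t-test** (ignoring the one degree of freedom spent on the covariate):

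| f | pre SD = 60√f | residual SD = 60√(1 − f) | 22 per group, 60 min | 32/33, 40 min |
|---|---|---|---|---|
| 0 | – | 60.0 | 90.0% | 75.4% |
| 10% | 19.0 | 56.9 | 92.7% | 79.6% |
| 20% | 26.8 | 53.7 | 95.2% | 84.1% |
| 30% | 32.9 | 50.2 | 97.2% | 88.5% |

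The 40 min in the last column is an assumption: 60 × (1 − 1/3), as if the one third not receiving the intended procedure contributed no difference, with the SD left at 60 min.

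**4. Check with the planned test.** Simulated Mann-Whitney power (normal times, 20,000 runs) at 22 per group is 88.5% with SD 60. It is 91.6, 94.1 and 96.4% with the residual SDs above. The pattern is the same.

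**5. If the one-hour SD covers only time after randomisation.** The total SD is then √(3600 + s²). For a pre-randomisation SD s of 20 min it is 63.2 min, and t-test power at 22 per group is 86.7%. For s = 30 min it is 67.1 min and 82.6%.

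**6. All 65 analysed with the full 60 min.** Power by normal approximation is 98.1%, and still 95.0% with a 30-min pre-randomisation SD added as in step 5. Without dilution there is little left to gain.

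**The case against.** The strongest reply is that nothing stated is wrong. The sample size section speaks of operating time. If its SD describes the whole operation, the pre-randomisation noise is already in it, and the planned power is met. That stands. A reader might infer from this point that the trial is underpowered, but the article does not support that: only the reading in step 5 produces a shortfall at 22 per group, and the article does not say that the SD excludes the early phase.

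A reader might also infer bias. There is none: the expected difference and the type I error are unchanged. Chance imbalance in early minutes is the same sampling variance, already allowed for in the test, and not a second harm.

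That the whole operation is timed is itself an inference, though the ordinary one. Clock definitions are details that an article may leave to the full protocol, so their absence is not the point here. Nor does the article say that surgery waits for pathology after a biopsy; no such delay is assumed.

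Finally, one might want to start the tested clock at the envelope. That would demote the length of operation that the Aim of the study names. Because the moment of randomisation varies, it could also be the noisier measure: if common steps fall before it in some patients and after it in others, early and late times are negatively correlated. Var(post) exceeds Var(total) when ρ < −SD(pre)/(2 SD(post)), which is −20/120 = −0.17 for SDs of 20 and 60 min. This objection stands against changing the clock. It does not touch adjustment, since Var(post)(1 − ρ²) is never larger than Var(post) or Var(total), whatever the sign of ρ.

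Adjustment does mean giving up the unadjusted Mann-Whitney test, which is a real change to the primary analysis.

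**Conclusion.** This is a cheap improvement and not an error. Read as total operating time, the gatekeeper endpoint carries minutes that cannot respond to treatment, and the planned test does nothing to remove them.

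The size of the gain cannot be derived from the article. Under assumed, independent variance shares of 10 to 30%, it is about 3 to 7 percentage points of power at 22 per group. If non-receipt also dilutes the difference to 40 min, it is about 4 to 13 points with 65 patients. Most of the deficit in that second case (about 75% power before any adjustment) comes from the assumed dilution and not from the timing of randomisation. With the full difference in all 65 patients, the gain is negligible.

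**What to change.** - Have the study nurse who already documents the operation in theatre record the time at which the envelope is opened.
- Keep total time from incision to closure as the first primary component, and state it so.
- Replace the unadjusted Mann-Whitney test in the Analysis section with a prespecified analysis adjusted for pre-randomisation minutes: a rank-based ANCOVA, or ANCOVA.
- Report time from randomisation to closure as a sensitivity analysis.

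The cost is one extra time stamp per patient and a slightly more complex primary test. The endpoint, the expected arm difference and the sample size need not change.
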